## Abstract

**Background:**

Acupressure therapy may be potentially beneficial in improving postoperative symptoms like postoperative nausea and vomiting (PONV), pain and sleep disorder and improving postoperative quality of recovery. The primary aim of this study is to investigate the efficacy of acupressure therapy on postoperative patient satisfaction and quality of recovery in hospitalized patients after surgical treatment.

**Methods/design:**

This three-group, parallel, superiority, blinded, randomized controlled trial will test the hypothesis that a combination of PC6, LI4 and HT7 acupressure is superior to sham or no intervention for improving postoperative quality of recovery in hospitalized patients. A minimum of 150 patients will be randomly allocated to one of the three experimental groups: control (no visit), light touch (sham acupressure) or active acupressure therapy in a 1:1:1 ratio. Interventions will be performed three times a day for 2 days. Patient satisfaction, quality of recovery, PONV and pain will be measured during the 3 days following randomization. The study protocol was approved by the Stony Brook University Institutional Review Board on 21 March 2016. Written informed consent will be recorded from every consented patient.

**Discussion:**

This study has the potential to improve the recovery of hospitalized patients by adding knowledge on the efficacy of acupressure therapy in this setting. A multipoint acupressure protocol will be compared to both a no intervention group and a light touch group, providing insight into different aspects of the placebo effect.

**Trial registration:**

ClinicalTrial.gov, NCT02762435. Registered on 14 April 2016.

**Electronic supplementary material:**

The online version of this article (doi:10.1186/s13063-017-1839-1) contains supplementary material, which is available to authorized users.

## Background

More than 200 million major surgical procedures are performed worldwide each year [1], and major advances have been made to decrease postoperative morbidity and mortality [2, 3]. These improvements in perioperative care have allowed for the emergence of other endpoints to assess improvement in perioperative care [4]. Patient-rated quality of recovery [5, 6] after surgery is gaining importance as a relevant endpoint in the study of perioperative care.

Application of pressure to specific external sites on the body has been practiced for hundreds of years and is generally recognized as a safe, cost-effective, non-invasive form of therapy with few to zero adverse effects [7, 8]. A meta-analysis studying the effectiveness of PC6 acupoint stimulation versus sham treatment or antiemetic drugs for the prevention of postoperative nausea and vomiting (PONV) including 59 trials [9] found a beneficial effect for PC6 acupoint stimulation versus sham treatment and no differences for PC6 acupoint stimulation versus antiemetic. This meta-analysis recommended further high-quality research on PC6 acupoint stimulation and on other acupoints. For pain treatment, a randomized controlled trial with a sample size of 129 patients [10] comparing acupressure and physical therapy for low back pain treatment showed a beneficial effect on pain scores in the acupressure group. A randomized controlled trial by Chen et al. [11] comparing acupressure versus no acupressure on sleep time and quality for intensive care unit patients (*n* = 85) showed beneficial effects in the acupressure group. The studied acupoints by Chen [11] were Neiguan (PC6), Shenmen (HT7) and Yongquan (K11) [12]. Anxiety improvement is also a studied field for acupressure therapy, and Beikmoradi et al. [13] showed that acupressure therapy including ear cavity, LI4, LI10, HT7, LU9, DU20, Ren6, Yintang and UB13 was beneficial compared to sham acupressure and control (*n* = 90).

Therefore, several studies suggest that acupressure therapy may be potentially beneficial in improving postoperative symptoms like PONV, pain and sleep disorder and improving postoperative quality of recovery. However, high-quality evidence to show the beneficial effects of acupressure therapy in postoperative quality of recovery care is lacking. For example, in a Cochrane meta-analysis on PONV [9], the primary outcome analysis on PC6 acupoint stimulation and antiemetic combination versus antiemetic alone was graded as very low quality due to heterogeneity, limitations and imprecision among the trials.

This three-group, parallel, superiority, blinded, randomized controlled trial will test the hypothesis that a combination of PC6, LI4 and HT7 acupressure is superior to sham treatment or no intervention for improving postoperative quality of recovery in hospitalized patients for surgical treatment. This therapy, if efficient, could help in improving quality of recovery following a large group of surgical procedures with few potential side effects.

## Methods/design

### Study design

The study is a three-group, parallel, superiority, randomized controlled trial (Fig. 1). Participants will be postoperative adult inpatients. The tested intervention will be PC6, LI4 and HT7 acupressure therapy. The main outcome will be quality of recovery with secondary outcome assessments of patient satisfaction, PONV and pain by the third postoperative day. The use of two comparator groups, i.e. a sham (light touch) group and a no intervention group (control group), will allow the assessment of different aspects of the placebo effect, including behavioural aspects (visiting and interacting with the patient) [14]. Research team members obtaining survey and other outcome data will not be told the allocated group identities. The study design aims at fulfilling the Standard Protocol Items: Recommendations for Interventional Trials [15] (Additional file 1: SPIRIT 2013 checklist) and the Revised Standards for Reporting Interventions in Clinical Trials of Acupuncture (STRICTA): extending the CONSORT Statement [16].

**Fig. 1 Fig1:**
[figure not shown]
The Consolidated Standards of Reporting Trials (CONSORT) flow diagram template for the AcuPressure to improve Patient satisfaction and quality of Recovery (APPROVE) study

### Setting and population

After Institutional Review Board approval, ClinicalTrials.gov registration and written informed consent, adult study patients will be enrolled. One hospital site will be involved in the study reflecting homogenous perioperative care. Only surgical patients expected to stay at least 2 days at the hospital after surgery and able to answer the study questions will be included. Recruiting time is planned to take 4 months.

### Sample size

Sample size calculations were carried out using SAS© 9.4 software, SAS, Cary, NC, USA. Based on results from a study examining the psychometric properties of the quality of recovery (QoR-15) evaluation [6, 17], we estimate the overall change from baseline to follow-up in untreated patients will be approximately 5% of the instrument total, or +7.5 points. We powered the study to be able to detect a clinically relevant change of 10% (+15 points) in the treatment group, with a standard deviation of 12 points. The primary hypothesis is a better quality of recovery in patients randomized to the active acupressure intervention group. A sample size of 50 subjects per arm (150 total) was calculated based on a two-sample *t* test for mean difference, with power = 0.85, alpha = 0.05. We have requested a total of 200 patients consented in order to allow for some screen failures that will inevitably occur, e.g. cancelled surgery.

### Recruitment

Patients will be screened at an academic center, the Stony Brook Medicine Hospital (Stony Brook, NY, USA) by a research team member. Those meeting all the inclusion criteria and none of the exclusion criteria will be introduced to the study. If interested, patients will be provided with complete information about the study including explanation, information sheet and clarification of any questions. Contact information for future questions will be provided and written informed consent recorded.

Inclusion criteria are English-speaking patients at Stony Brook Medicine Hospital who are expected to stay in the hospital for at least 2 days and are able to provide written informed consent.

Exclusion criteria are as follows: patients younger than 18 years of age; those who do not have access to the three points on the hand and wrist due to skin breakdown, ulcers, cellulitis, broken bone, indwelling catheter within 5 cm radius of the pressure points, etc. (since the plan is to apply the pressure unilaterally, this exclusion only applies if the issue that is preventing pressure to be applied exists on both extremities); significant dementia or altered mental status that would prevent assessment of the QoR-15 survey; allergic reaction to ink from a Sharpie pen; stroke or other neurologic condition which precludes sensation in both upper extremities; use of regional anaesthetic technique, e.g. epidural, continuous peripheral nerve catheter, after postoperative day 1 at 12 noon; women who are currently pregnant, screened via urine pregnancy test.

**Fig. 2 Fig2:**
[figure not shown]
APPROVE study schedule of enrolment, interventions and assessments

### Concurrent treatment

All patients will receive routine care. To assess balance between the three groups in potential confounders, variables such as age, sex, comorbidities, type of surgery, type of anaesthesia, type of anaesthetic agents, prophylactic antiemetics and sleep aids will be recorded. Clinicians involved in routine patient care will be blinded to study group assignment.

### Outcome measures

Data will be collected using an electronic case report form and a few written forms created to maintain blinding of the assessors. The primary endpoint will be the change in the established quality of recovery (QoR)-15 score [6]. The QoR-15 is a 15-question survey measuring patient satisfaction/quality of recovery including pain, nausea, sleep and well-being. Each question is rated on a Likert scale from 0 to 10. The maximum score of the QoR-15 is 150 points, indicating ideal health status. This score will be assessed by a research team member on study day 0 between 7:30 and 8:30 am prior to first intervention and on study day 3 between 7:00 and 10:00 am. If the patient is discharged from the hospital before study day 3, the QoR-15 score will be completed by telephone.

Secondary endpoints include individual measures of pain, nausea and patient satisfaction, using a numeric rating scale, and vomiting that will be assessed on study days 0 (between 7:30 and 8:30 am, i.e. before the first intervention), 1 and 2 (between 3:00 and 4:00 pm). Patient opinion about acupressure effect will be assessed on study day 0 between 7:30 and 8:30 am prior to the first intervention and on study day 2 between 7:00 and 10:00 am.

Other secondary endpoints will be recorded daily from the patient medical record, including sleep aids, antiemetic administration, opioid and non-opioid consumption, episodes of delirium and hospital length of stay. A research coordinator will monitor accuracy of the data in randomly sampled case report forms by comparing hospital source documents with data in the electronic case report form. QoR-15 scores will be recorded on paper case report forms and later entered into an MS Access© database. Study documents will be stored in a locked cabinet. Study team members will have access to the final trial dataset.

### Data analysis

#### Analysis plan

This is a randomized, single-blinded controlled trial. The study will be analysed in four ways. The primary method of analysis will use the modified intention to treat (mITT) approach, with the treatment group incurring at least one treatment session. Patients who obtain the baseline measurement and are randomized to the treatment group but do not receive at least one treatment will be excluded from the analysis. Otherwise, missing data will be accounted for using a multiple imputations method [20]. In addition, if data are missing at random, a secondary sensitivity analysis will be conducted that excludes patients with missing follow-up data, but includes patients who did not complete the entire treatment regimen (follow-up complete, FC). A tertiary adherers-only (AO) analysis may be included to examine the subset of patients who fully received the treatment to which they were randomized and completed both baseline and follow-up assessments. We will also perform an ITT analysis.

#### Statistical analysis

The primary outcome of this study is the QoR-15 change score from baseline to follow-up on day 3. Mean change score between the control group (no intervention) and the acupressure treatment group will be assessed for differences using either the Student’s *t* test or Wilcoxon rank sum test. We do not expect to see any significant differences between the two groups regarding age, sex, American Society of Anesthesiologists (ASA) status, surgical duration, anaesthetic technique, intraoperative fluid therapy volume, postoperative day 1 Sequential Organ Failure Assessment Score [21] and other comorbidities due to the randomization process; however, we will examine the groups for differences. Additional event metrics (e.g. antiemetic medication consumption and opioid consumption (including amount)) during the study period will also be collected and analysed. Event variables that differ significantly between groups may be used as potential covariates in a multivariate linear regression. The statistician will remain blinded to the group assignment for the analyses.

Finally, for all four methods of analysis (mITT, FC, AO, ITT), secondary assessments for the placebo effect will be conducted. Analyses for differences in mean change QoR-15 score include comparisons between (1) the control vs. sham group and (2) the sham group vs. the active acupressure group.

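### Adding baseline QoR-15 to the primary analysis (ANCOVA) would be a nearly free gain over the valid but less efficient unadjusted change-score test

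*Protocol article*

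**What the plan says.** Under Statistical analysis the article defines the endpoint: "The primary outcome of this study is the QoR-15 change score from baseline to follow-up on day 3". Mean change in the control and acupressure groups "will be assessed for differences using either the Student’s *t* test or Wilcoxon rank sum test". The text gives no rule for choosing between the two tests and no covariate.

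Under Outcome measures the QoR-15 is scheduled "on study day 0 between 7:30 and 8:30 am prior to first intervention and on study day 3 between 7:00 and 10:00 am", so a pre-intervention score is planned for each patient.

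The only adjustment mentioned is optional: "Event variables that differ significantly between groups may be used as potential covariates in a multivariate linear regression". Its examples are antiemetic and opioid consumption during the study period, which arise after randomisation. Baseline QoR-15 is not named there, nor among the characteristics to be compared between groups.

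Under Sample size the expected change in untreated patients is "approximately 5% of the instrument total, or +7.5 points", and the trial is powered for a "clinically relevant change of 10% (+15 points) in the treatment group, with a standard deviation of 12 points". The calculation uses a two-sample t test with power 0.85 and alpha 0.05, and gives 50 per arm. Under Analysis plan, multiple imputation belongs to the primary modified intention-to-treat analysis. Under Randomization and allocation concealment, allocation is stratified by use of postoperative regional anaesthesia.

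**The concern.** The baseline value of an outcome is usually its strongest predictor, and here it enters only by subtraction. Subtraction is the same as fitting a regression on baseline with the slope fixed at 1. The true slope is rho x SD(day 3) / SD(day 0), where rho is the correlation between the two scores. If that slope is below 1, subtraction over-corrects: the arm that happens to start lower appears to gain more, and the variance is larger than it need be.

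Two further features point the same way. The t test and the rank sum test address different hypotheses, and the second gives no estimate of the mean difference for which the trial was sized. A regression coefficient and its standard error also pool directly over imputations by Rubin's rules, whereas a rank sum result needs extra steps.

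At stake are the width of the primary confidence interval and how far one trial's result depends on chance differences at the start. The comparisons with sham also use change scores and have no power calculation of their own, so precision may matter more there.

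**Working it through.** **Inputs from the article.** Difference 15 - 7.5 = 7.5 points; SD 12; 50 per arm; alpha 0.05; power 0.85.

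**Assumptions, not in the article.** The test is two-sided; SD 12 is the SD of the change; rho is 0.3 to 0.8; the SDs at day 0 and day 3 are equal, except in step 5.

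**1. The plan's own figure.** The normal approximation gives n = 2 x (1.960 + 1.036)² x (12/7.5)² = 2 x 8.98 x 2.56, about 46 per arm; the exact t calculation gives 47. The stated 50 is slightly more than the formula needs. Power at 50 per arm is 0.872 (exact t), above the stated 0.85. The small gap is on the safe side and does not bear on this point.

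**2. Variance under ANCOVA.** With equal SDs, Var(ANCOVA)/Var(change) = (1 - rho²) / [2(1 - rho)] = (1 + rho)/2. The SE of the change-score difference is 12 x sqrt(2/50) = 2.40.

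| Analysis | Variance ratio | Effective SD | SE of difference | Power at 50 per arm | n per arm for 0.85 (normal) |
|---|---|---|---|---|---|
| Change score | 1 | 12 | 2.40 | 0.87 | 46 |
| ANCOVA, rho 0.3 | 0.65 | 9.67 | 1.93 | 0.97 | 30 |
| ANCOVA, rho 0.5 | 0.75 | 10.39 | 2.08 | 0.95 | 35 |
| ANCOVA, rho 0.7 | 0.85 | 11.06 | 2.21 | 0.92 | 40 |
| ANCOVA, rho 0.8 | 0.90 | 11.38 | 2.28 | 0.90 | 42 |

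**3. Simulation check (20,000 trials per rho, 50 per arm).** Power of the change-score test against ANCOVA was 0.874 against 0.968 (rho 0.3), 0.871 against 0.943 (rho 0.5) and 0.871 against 0.916 (rho 0.7). The change-score estimate correlated with the chance baseline difference at -0.59, -0.50 and -0.39; for ANCOVA the correlation was about 0.

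**4. Baseline imbalance at rho 0.5.** A change SD of 12 implies a baseline SD of 12 / sqrt(2 x 0.5) = 12. The SE of the baseline difference is then 12 x sqrt(2/50) = 2.4. A difference of 3 points or more in either direction has z = 3/2.4 = 1.25, a chance of about 21%. It shifts the change-score estimate by (1 - 0.5) x 3 = 1.5 points, which is 1.5/2.4, about 0.6 of its SE.

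**5. When the gain vanishes.** Take rho 0.8 and a day-3 SD 1.25 times the baseline SD. The slope is 0.8 x 1.25 = 1. In units of the baseline variance, Var(change) = 1 + 1.5625 - 2 x 0.8 x 1.25 = 0.5625, and Var(ANCOVA) = 1.5625 x (1 - 0.64) = 0.5625. The two are the same.

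**The case against.** The strongest reply is that nothing here is an error. A t test on change between randomised arms is unbiased over randomisation and keeps its type I error. The sample size was computed for that test, and its power exceeds the stated 0.85. The 1.5-point shift is variation that the change-score SE already covers. All of this stands.

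A second reply is that the size of the gain rests on figures the article does not give: rho, the two SDs, and whether 12 is the SD of change. This also stands. The condition for over-correction is a slope below 1; a correlation below 1 is not enough, as step 5 of the working shows.

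A reader might infer more than the text supports:

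- **That the primary result will be biased or the trial underpowered.** The replies above rule this out.
- **That the test will be picked after the results are seen.** The article gives no selection rule, but it does not say the choice follows the results. It keeps the statistician blinded to group assignment, and a rule may stand in an analysis plan that is not shown.
- **That every patient will have a baseline score.** The article gives a schedule. Its adherers-only set requires completed baseline and follow-up assessments, so gaps are foreseen.

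The replies do not show that the plan already adjusts for baseline. The optional regression depends on significance, is aimed at post-randomisation event variables and does not name baseline QoR-15.

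**Conclusion.** The point stands as an improvement in efficiency and robustness; it does not correct an error. The planned change-score test can be defended and has about 0.87 power at 50 per arm. With equal SDs, SD 12 as the SD of change and rho between 0.3 and 0.8, baseline adjustment cuts the variance by 35% to 10% and raises power to between 0.97 and 0.90. It also removes the dependence of the estimate on chance baseline differences. If the slope is near 1 the gain is negligible, but adjustment then costs almost nothing. The direction of the benefit is secure for any slope other than 1; its size is not known from the article.

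**What to change.** Prespecify one primary linear model: day-3 QoR-15 on allocated arm, baseline QoR-15 and the regional-anaesthesia randomisation stratum. Report the adjusted mean difference between acupressure and control with its 95% CI, pooled over imputations by Rubin's rules. The change score may remain the named endpoint, because regressing change on the same terms gives the identical treatment effect. Keep the unadjusted t test and the Wilcoxon test as sensitivity analyses.

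No new data or patients are needed, and the model uses a couple of degrees of freedom. Since screening began on 28 March 2016, the change should be a dated, documented amendment to the analysis text, made before unblinding.

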## Discussion

### Acupressure intervention

We selected three acupoint locations, based on recommendations by the World Health Organisation [12]. These points are commonly used for treating symptoms that may improve quality of recovery like PONV, pain and sleep disturbance. These acupoint locations will be marked accordingly on every patient before randomization to improve the standardization of the intervention and decrease the hazard of measurement bias.

Multipoint acupressure [22–25] was preferred over single point acupressure to increase the likelihood of triggering a beneficial signal. The combination of multiple acupressure points was shown to be beneficial for ventilator-induced anxiety and dyspnoea [22], for prehospital analgesia in patients with radial fractures [25] and for prehospital analgesia in patients with minor trauma [26].

We chose to apply acupressure for 2 minutes on each point at each session. This duration has already been used in published randomized controlled trials reporting beneficial effects of acupressure therapy. Wang and colleagues reported beneficial effects on self-assessed quality of life for hemodialysed patients [27] using 2 minutes of pressure on auricular acupoints. Similary, Pouresmail described positive effects of 2 minutes of acupressure on primary dysmenorrhea [28]. Yang et al. [29] reported favourable effects of 2 minutes per point acupressure associated with aromatherapy on dementia-associated agitation.

The frequency of the intervention was set as three times a day, similar to previously published studies, including those of Chang et al. for postoperative pain after total knee replacement [30] and Shin et al. for hyperemesis gravidarum [31].

The treatment will be administered for 2 days, which was a balance between more sessions (i.e. 6 days) that might confer more benefit with a need to limit the sessions to a period of time when these hospitalized patients would still be available for the study interventions.

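### An optional, unlabelled regression may adjust for on-study antiemetic and opioid use because these differ between arms; read as the treatment effect, it would not estimate the total effect of acupressure

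*Protocol article*

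**What the plan says.** All references are to the protocol article.

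- **Primary outcome and comparison (Statistical analysis).** The outcome is how far QoR-15 moves between baseline and day 3. On the comparison, the section says: "Mean change score between the control group (no intervention) and the acupressure treatment group will be assessed for differences". The named method is a t test or a Wilcoxon test, and no covariates enter it.
- **Event metrics (same section).** After a sentence on baseline and perioperative characteristics, the text continues: "Additional event metrics (e.g. antiemetic medication consumption and opioid consumption (including amount)) during the study period will also be collected and analysed".
- **Covariate rule (next sentence).** "Event variables that differ significantly between groups may be used as potential covariates in a multivariate linear regression". The section does not name the dependent variable of this regression or give its status relative to the t or Wilcoxon test.
- **The same variables as endpoints (Outcome measures).** "Other secondary endpoints will be recorded daily from the patient medical record, including sleep aids, antiemetic administration, opioid and non-opioid consumption".
- **Content of the primary score (Outcome measures).** "The QoR-15 is a 15-question survey measuring patient satisfaction/quality of recovery including pain, nausea, sleep and well-being".
- **Rationale for the acupoints (Discussion, Acupressure intervention).** "These points are commonly used for treating symptoms that may improve quality of recovery like PONV, pain and sleep disturbance".

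**The concern.** Randomisation precedes the first session, so drug use during the study period is measured after allocation and can be changed by it. On the article's own rationale, acupressure acts on nausea, pain and sleep. These symptoms drive antiemetic, opioid and sleep-aid use, and they are also part of the QoR-15. Antiemetic and opioid use may therefore lie on the path from treatment to the primary outcome, or share causes with it.

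In a randomised trial, a significant difference between arms in such a variable points to a treatment effect (or chance), not to confounding that needs correction. The rule selects covariates on exactly that signal. A model that holds drug use fixed asks a different question: what acupressure does to recovery other than through drug use. Even that question is answered properly only if nothing unmeasured drives both drug use and recovery.

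Two further features add to the problem. The rule is permissive and depends on p-values, so the model is settled after the data are seen. And because the regression has no stated status, a reader of the results could not tell which estimate is the treatment effect. Blinding the statistician does not help, since the trigger works equally well on coded arms.

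**Working it through.** **Inputs from the article (Sample size).** Expected change is +7.5 points untreated and +15 treated, so the difference is 15 − 7.5 = 7.5. SD is 12, n is 50 per arm, alpha is 0.05 (two-sided assumed) and stated power is 0.85.

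**The plan's own figure.** The standardised difference is 7.5/12 = 0.625. A two-sample t test with power 0.85 needs 46.95, so 47 per arm. The stated 50 is slightly conservative and gives power of about 0.87. Nothing below depends on this gap.

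**Assumptions not in the article.** A drug-use variable M has within-arm SD 1 and is lower by a = 0.5 SD under acupressure. Lower M goes with better recovery, and a share s = 20%, 30% or 50% of the 7.5 points runs through M. No unmeasured factor drives both M and QoR-15 change. Whenever the trigger is met, the adjustment is made.

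**Always adjusting.**

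- Expected adjusted estimate = 7.5 × (1 − s).
- Slope on M: b = 7.5 × s / 0.5.
- Residual SD = √(144 − b²).
- Approximate SE = residual SD × √(2/50) × √(1 + a²/4), where √(2/50) = 0.2 and √1.0625 = 1.031.

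| s | b | residual SD | SE | estimate | estimate/SE |
|---|---|---|---|---|---|
| 20% | 3.0 | √135 = 11.6 | 2.40 | 6.0 | 2.5 |
| 30% | 4.5 | √123.75 = 11.1 | 2.29 | 5.25 | 2.3 |
| 50% | 7.5 | √87.75 = 9.4 | 1.93 | 3.75 | 1.9 |

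Simulation agrees: about 6.0, 5.2 and 3.7 points, with power about 0.69, 0.61 and 0.47.

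**Adjusting only when M differs at p < 0.05, which is the rule as written.** A 0.5 SD difference with 50 per arm is significant in about 70% of trials. Simulating the whole procedure gives:

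| s | mean estimate under the rule | power under the rule | unadjusted estimate | unadjusted power |
|---|---|---|---|---|
| 20% | about 6.2 | about 0.72 | 7.5 | about 0.87 |
| 30% | about 5.6 | about 0.65 | 7.5 | about 0.87 |
| 50% | about 4.3 | about 0.53 | 7.5 | about 0.87 |

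**How often the rule fires.** With drug use lower by 0, 0.3, 0.5 or 0.8 SD, it fires in about 5%, 31%, 70% or 98% of trials. At 0 the mean estimate stays at 7.5.

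**No total effect on QoR-15, drug use lower by 0.5 SD.** With a within-arm correlation of −0.3 or −0.5 between drug use and QoR-15 change, the adjusted mean is about −1.8 or −3.0 points. The rule then rejects in about 9% or 21% of trials, against about 5% unadjusted. So the rule can also create an apparent effect where there is no total effect.

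**The case against.** The strongest reply is that the primary analysis is untouched. The section names an unadjusted t or Wilcoxon test first, the sample size rests on the two-sample t test, and the regression follows later in doubly tentative wording. This stands. A reader might infer that the plan adjusts the primary comparison itself, or that the trial's power falls to the adjusted figures. The text supports neither: the unadjusted result is produced whatever happens, and the lower power belongs to the optional regression. That QoR-15 change is its dependent variable is the natural reading, but still an inference.

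A reader might also infer that the rule removes the effect exactly when the treatment works. That is too strong. The rule fires when drug use differs, not when QoR-15 improves; if acupressure improves recovery without changing drug use, it fires only by chance, in about 5% of trials. Nor is attenuation certain: if the drugs themselves raise QoR-15, or an unmeasured factor drives both, the bias could run the other way.

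Finally, a fuller analysis plan may define the regression's role. That answers only part of the point. The article does not merely leave the covariates open; it states a selection rule, and the rule is unsound as stated. The preceding sentence already deals with baseline characteristics, so the rule cannot fairly be read as baseline adjustment.

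**Conclusion.** The concern holds for the optional regression, not for the primary test. The article permits a model of unstated status to adjust for post-randomisation variables that it also lists as secondary endpoints, and selects them because the arms differ. Read as the treatment effect, that model does not estimate the total effect of acupressure, whichever way the bias runs.

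The size depends on inputs the article does not give. In the illustration, a 7.5-point effect becomes about 6.2 down to 4.3 points under the rule. The loss is small if little of the effect passes through drug use, and absent on average if acupressure does not change drug use. The point should be fixed; it is not a fatal flaw, because the unadjusted comparison stands.

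**What to change.** In Statistical analysis, delete the sentence that makes event variables covariates according to whether they differ significantly between groups. In its place, state that:

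1. the unadjusted comparison of QoR-15 change between acupressure and control is the primary analysis;
2. any adjusted model of the treatment effect uses only variables fixed before randomisation and named in advance, for example baseline QoR-15 and the regional-anaesthesia stratum;
3. antiemetic, opioid and sleep-aid use are analysed as outcomes;
4. any model that includes them as covariates is exploratory and is not an estimate of the treatment effect.

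The two covariates in item 2 are examples; the cure lies in naming pre-randomisation variables in advance, not in that particular pair. The cost is wording only: no added patients, visits or data, and drug use is still reported as planned.
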